## Compensation

Study subjects will receive a total of $200 if they participate in the entire study. A check will be mailed to their home within a month after each visit. Study subjects will receive $20 for visits at weeks -4, 0, 2, 4, 16, 28, 41 and the postop visit and $40 for the visit at week 16.

# MEASUREMENT OF EFFECT

Although the clinical benefit of these drug(s) has not yet been established, the intent of offering this treatment is to provide a possible therapeutic benefit, and thus the patient will be carefully monitored for AIN regression, HPV viral presence/absence through genotyping and symptom relief in addition to safety and tolerability. **Patients undergoing anal cytology and HRA evaluation will be receiving standard of care surveillance through these surveillance strategies.**

- - 1. Methods for Evaluation of Measurable Disease
- **Anal cytology and HRA**: determine regression from AIN III to AIN I or no evidence of AIN.
- **HPV viral genotyping**: determine efficacy of Artesunate suppository by the eradication of HPV.

# DATA REPORTING / REGULATORY REQUIREMENTS

Adverse event lists, guidelines, and instructions for AE reporting can be found in Section 6.0 (Adverse Events: List and Reporting Requirements).

## Data Reporting

The frequency and severity of all toxicities will be tabulated from CRFs and summarized for review in a descriptive fashion. All CRFs will be reviewed by the principal investigator on a weekly basis with the research team. The initial review of toxicity will be completed after the first treatment group has completed the intervention portion of the study.

Data collected at study visits at both institutions will be entered into the study REDCap database housed at Johns Hopkins.

The secondary efficacy endpoints will be compared with analogous data obtained in an open prospective database, “Development of a Prospective HRA Database” (Johns Hopkins IRB# [NA_00078993](https://e-irb.jhmi.edu/eirb2/Rooms/DisplayPages/LayoutInitial?Container=com.webridge.entity.Entity%5BOID%5B1E381BBFC925834D936BB3B006F85B94%5D%5D) ). This observational cohort protocol has been open since 2012 and includes over 250 subjects. These subjects are all of the patients that have been treated with HRA and ablation in the Johns Hopkins HRA Clinic. We will compare changes in HPV viral load and AIN pathology from baseline to HRA evaluation at 16, 28, and 40 weeks.

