| **Statistical Methods**:   1. **Definition of primary outcome/endpoint:** This is a Phase I modified 3 + 3 design, in which the MTD will be identified. 2. **Definition of secondary outcomes/endpoints:**  - Downgrade in AIN 2/3 to AIN 1 or no AIN - HPV genotype testing—optimally to undetectable levels of HPV at week 40 of follow. - Creating of tissue bank for future studies.   **Analytic plan for primary objective:** This is a Phase I modified 3 + 3 design, in which the MTD will be identified. Based on previous studies of rectally administered Artesunate for the treatment of malaria, the safety profile demonstrates a low probability of dose limiting toxicity in children, as well as adults. The initial dose will be a 200 mg suppository administered in cycles of 5 daily doses at weeks 0 and 2. Dose escalation will proceed with a 3 + 3 design with the safeguard of an integrated de-escalation schema. At the MTD, an expansion cohort of 12 patients will be included.  Note: Each cycle = 5 days   | **Dose Escalation Design** | | | | | | --- | --- | --- | --- | --- | | **Cohort** | **Dose (mg)** | **Number of Treatment Cycles** | **Designated Weeks of Artesunate Administration** | **Number of patients** | | **I** | 200 | 2 | 0, 2 | 3 | | **II** | 200 | 3 | 0, 2, 4 | 3 | | **III** | 400 | 2 | 0, 2 | 3 | | **IV** | 400 | 3 | 0, 2, 4 | 3 | | **V** | 600 | 2 | 0, 2 | 3 | | **VI** | 600 | 3 | 0, 2, 4 | 3 |   ***According to the standard of care clinical practice, a postoperative visit will be done 4 weeks after ablation, i.e. either on week 20 or on week 32   1. **Analytic plan for secondary objectives:**     1. For the dichotomous variables of regression of AIN 2/3, counts, percents and 95% confidence levels will be calculated.    2. HPV viral genotyping will be assessed to determine when HPV viral load will become undetectable.    3. Tissue bank of specimens for future studies. 2. **Sample size justification:** In this phase I dose escalation trial, 6 dose levels will be considered for a total sample size of 36-60 patients with a target dose limiting toxicity (DLT) of < 18%. |
| **Funding, Regulatory, and Feasibility Issues:**  Frantz Viral Therapeutics will supply the Artesunate suppositories at no cost. The suppository will be obtained from an off-site pharmacy (Buderer Drug Company).  Buderer Drug Company will ship suppositories to the Johns Hopkins Hospital Investigational Drug Pharmacy for each patient enrolled in the study. |

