## Definition of Dose-Limiting Toxicity

A dose-limiting toxicity (DLT) is defined as any drug-related Grade 2 (moderate; minimal, local, or noninvasive intervention indicated; limiting age appropriate instrumental ADL) or greater drug-related toxicities in any organ system (or Grade 3 or greater toxicities–severe or medically significant but not immediately life-threatening; hospitalization or prolongation of hospitalization indicated; disabling; limiting self care ADL**) in any organ system (including gastrointestinal, dermatologic, and neurologic), as delineated in Common Terminology Criteria for Adverse Events v4.0 (CTCAE).

This above definition of dose-limiting toxicity applies to the drug that is being studied—the artesunate suppository. Post-procedural complications related to the HRA procedure are not dose limiting.

The dose limiting toxicity determining period for the study will extend to 1 week after the last cycle of artesunate suppository. Thus, for the 2 cycles, the DLT determining period will extend to 3 weeks; for 3 cycles, it will extend to 5 weeks.

Beyond the DLT determining period, if patients in a specific cohort have complete resolution of their high-grade dysplastic lesions, then the plan will be to stop at this dosing cycle and frequency and move into the 12-patient expansion cohort.

Management and dose modifications associated with the above adverse events are outlined in Section 6.

Dose escalation will proceed within each cohort according to the modified 3+ 3 design with de-escalation schema and an expansion cohort at MTD. Dose-limiting toxicity (DLT) is defined as above.

The specific details are as follows,

The 3 + 3 dose escalation will consist of 6 dose levels in combination with variation in dosing schedules the single agent Artesunate, with additional de-escalation steps. An expansion cohort of 12 patients will be included at the MTD. Once MTD is found, then secondary outcomes will be evaluated. In MTD expanded patient cohort, anal intraepithelial neoplasia (AIN) regression from AIN 2/3 to low-grade anal intraepithelial neoplasia (AIN 1) or no residual AIN will be assessed through subsequent HRA evaluation. Cytology specimens will be tested through quantitative PCR for HPV viral load during initial and subsequent HRA evaluations. A tissue bank will be created for future studies.

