## Analysis of Primary and Secondary Endpoints

- - 1. Analysis of safety endpoints

The NCI common terminology criteria for adverse events (AE) (CTCAE 4.0) will be used to evaluate toxicity. We will consider a toxicity to be an adverse event that is possibly, probably or definitely related to treatment. The maximum grade of toxicity for each category of interest will be recorded for each patient, and the summary results will be tabulated by category, grade, and dose level. Serious (≥ Grade 3) toxicities will be described on a patient-by-patient basis and will include any relevant baseline data.

Once the MTD (or RP2D) is found, then secondary outcomes will be evaluated based on MTD.

- - 1. Analysis of secondary efficacy endpoints

Regression of AIN 2/3 to either AIN 1 or the absence of AIN will be used as dichotomous variables and the proportion of patients with the characteristics and the corresponding 95% confidence intervals will be calculated.

HPV viral genotype will be collected longitudinally over time as a qualitative measure.

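### The planned comparison with an all-ablated database cannot isolate artesunate at weeks 28 and 40, because trial patients with persistent disease are ablated too, and the HPV measure to be compared is contradictory

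*Protocol*

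**What the plan says.** Section 10.1 (Data Reporting) commits to an external comparison: "The secondary efficacy endpoints will be compared with analogous data obtained in an open prospective database". On size and period it says: "This observational cohort protocol has been open since 2012 and includes over 250 subjects". On who is in the database: "These subjects are all of the patients that have been treated with HRA and ablation in the Johns Hopkins HRA Clinic". On what is compared and when: "We will compare changes in HPV viral load and AIN pathology from baseline to HRA evaluation at 16, 28, and 40 weeks".

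Inside the trial, the Synopsis schema sends patients with no improvement at week 16, and those with AIN2/3 at week 28, to ablation in the operating room. Section 8.3.8 likewise ablates residual disease seen at either visit. Table 1 in section 8.2 places excision after the week 16 HRA. The Synopsis calls ablation the standard of care and lets a patient choose surgery at any time.

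Section 14.3 plans only the proportion of patients regressing to AIN 1 or no AIN, with 95% confidence intervals. It does not mention the database. On HPV it says: "HPV viral genotype will be collected longitudinally over time as a qualitative measure".

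**The concern.** Section 10.1 calls the database analogous, but the two groups are managed differently up to week 16 and partly alike after it. In the database, a change in pathology reflects ablation and any recurrence. In the trial, it reflects artesunate up to week 16, and after that artesunate in some patients and ablation in the rest. A similar AIN2/3-free rate at week 28 or 40 could then be read as the drug matching surgery when surgery produced it.

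Two features add to this. The database is open, and it covers all ablated patients of a clinic that also recruits for the trial. Patients with recurrence after surgery are eligible, and trial patients ablated there would fit its definition. The protocol states no exclusion, so one person could be counted on both sides. The second site has no counterpart in the database.

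The HPV part of the comparison is on viral load, while other sections describe an assay that gives no load.

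**Working it through.** **1. No stated figure to reproduce.** The protocol gives no alpha, margin, effect size or power for this comparison. The numbers below are illustrations under stated assumptions.

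**2. Mixing of drug and ablation effects.** Let r be the proportion regressing on artesunate and a the AIN2/3-free proportion after ablation. Assume that all non-regressors have been ablated by the time of assessment, that regressions last, and that a is the same in the trial and the database.

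- Week 16, before planned ablation: difference = r − a.
- Week 40: the trial shows r + (1 − r)a and the database shows a, so difference = r(1 − a).

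Values of a: section 2.1 gives recurrence after ablation of up to 50% within one year in HIV-negative patients, and up to 68% in HIV-positive patients with no time frame. Hence 1 − 0.50 = 0.50 and 1 − 0.68 = 0.32. Because these recurrence figures are maxima, 0.80 is added as an assumed higher value. The values of r are assumed.

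| a | r | Week 16 difference | Week 40 trial rate | Week 40 difference |
|---|---|---|---|---|
| 0.32 | 0 | −0.32 | 0.32 | 0 |
| 0.32 | 0.20 | −0.12 | 0.46 | +0.14 |
| 0.32 | 0.40 | +0.08 | 0.59 | +0.27 |
| 0.50 | 0 | −0.50 | 0.50 | 0 |
| 0.50 | 0.20 | −0.30 | 0.60 | +0.10 |
| 0.50 | 0.40 | −0.10 | 0.70 | +0.20 |
| 0.80 | 0 | −0.80 | 0.80 | 0 |
| 0.80 | 0.20 | −0.60 | 0.84 | +0.04 |
| 0.80 | 0.40 | −0.40 | 0.88 | +0.08 |

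With r = 0 the week 40 difference is 0 for every a. The same holds at week 28 if an inert drug brings no improvement and the ablations that follow week 16 have been done by then. With a = 0.50 and r = 0.20, the drug alone is 30 points below ablation at week 16, yet the trial group is 10 points above it at week 40. The sign changes because of the trial's own ablations.

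**3. Precision at week 16.** Section 14.1 allows a total of 12 patients at the MTD. If 6 of 12 regress, the exact (Clopper-Pearson) 95% interval is 21.1% to 78.9%. For an assumed 30% against 50%, the standard error is √(0.3 × 0.7/12 + 0.5 × 0.5/250) = 0.136, and the 95% half-width is 1.96 × 0.136 = 0.267, about 27 points. Power for 12 against 250 at an assumed two-sided 0.05 is 26% for 0.70 v 0.50, 54% for 0.80 v 0.50 and 89% for 0.90 v 0.50.

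**4. The HPV measure, place by place.**

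- Synopsis, secondary objectives: Hybrid Capture 2 DNA testing. Section 1.2 has genotype testing for the same objective.
- Synopsis, analytic plan: "HPV viral genotyping will be assessed to determine when HPV viral load will become undetectable".
- Section 5.2, in the paragraph on the MTD expansion: "Cytology specimens will be tested through quantitative PCR for HPV viral load during initial and subsequent HRA evaluations".
- Section 9: "HPV viral presence/absence through genotyping".
- Section 10.1: change in viral load.
- Section 14.3: a qualitative genotype.

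A presence/absence or qualitative result cannot give a change in load; quantitative PCR can. Nothing in the protocol says that the database holds matching loads.

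**The case against.** The strongest reply is that ablation is the standard of care and that the drug is meant to spare patients surgery, so an ablated cohort is a relevant external reference. Section 10.1 never presents it as an untreated control and uses no inferential language. Matching, exclusions and stratification may sit in an analysis plan that is not shown, and 14.3 already plans single-group proportions. These are secondary endpoints of a phase I dose-finding trial.

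Much of this stands, and it rules out several stronger readings that a reader might infer:

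- That the comparison says nothing about artesunate. Week 16 comes before planned ablation, so its pathology contrast does set artesunate against ablation, crudely.
- That an active drug could look worse than no drug. The comparator is surgery, and falling short of surgery is a different statement.
- That the HPV comparison cannot be computed. Section 5.2 plans quantitative PCR for viral load, so the defect is a contradiction between sections.
- That loss of the genotypes present at screening is the endpoint really measured. The protocol defines no such endpoint.
- That database patients were all ablated at their baseline, that trial patients are in fact in the database, or that HIV status confounds the contrast. Section 10.1 does not date the ablations, and the database protocol is not available. Overlap and confounding are possible but unconfirmed.

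The reply does not rescue weeks 28 and 40. Section 10.1 fixes the comparison at those times, and the trial's own ablation pathway removes its meaning as evidence on the drug. Matching or adjustment of baseline factors would not undo that.

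**Conclusion.** The point holds in limited form. Followed as written, the week 28 and 40 pathology comparisons mix drug and ablation effects and cannot isolate artesunate. An inert drug would show a difference of 0 from ablation at week 40 for any ablation success rate, provided that non-regressors are ablated and that ablation works equally well in both groups. Week 16 remains usable, but only as a non-randomised contrast with ablation in about 12 patients, with a half-width of roughly 27 points in the example above. It gives no effect against untreated disease, and it is protected only for patients who have not already opted for surgery.

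Separately, the HPV measure is contradictory across the Synopsis and sections 5.2, 9, 10.1 and 14.3, and the comparison in 10.1 has no counterpart in 14.3. The regression rates, the 0.80 value and the 0.05 level are assumptions; the 0.50 and 0.32 values come from maximum recurrence figures that are not tied to weeks 16 to 40. The conclusion for r = 0 does not depend on the value of a. The plan should be changed on this point; the primary safety objective is not affected.

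**What to change.** - **Section 10.1, week 16:** limit the database comparison to this visit, before any trial ablation. Label it a descriptive, non-randomised contrast with ablation as standard of care, and exclude trial participants from the database side.
- **Weeks 28 and 40:** report only the single-arm regression proportion with 95% confidence interval already planned in 14.3. Count patients ablated in the trial as not regressed on artesunate. State that the database is not used as evidence of drug effect at these visits.
- **HPV:** reconcile the measure across the Synopsis (secondary objectives and analytic plan) and sections 5.2, 9, 10.1 and 14.3. Compare viral load only if quantitative PCR is done in the trial and the database holds matching data.
- **Alignment:** make 10.1 and 14.3 describe the same analyses.

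The cost is wording. No patients, visits or procedures are added. The sponsor gives up the later external comparisons, and counting ablated patients as not regressed is conservative towards the drug.

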**10.2 Risks to privacy of individuals, confidentiality of data**

There is a potential risk of loss of confidentiality. To ensure that all information and specimens collection remain confidential and anonymous, all study data will be de-identified. Only the research team will have access to study participant private data. All study study specimens are de-identified and cannot be linked to the subjects. Specimens will be barcoded before storage so that patient identifiers will not be available to the laboratories performing the assays proposed in this application.

To ensure that all study data remains confidential, all study data will be maintained on an encrypted password-protected database. Patient identifying information will not be associated with the study research data. Only the research investigators will be able to access a list connecting patient identifiers with the study ID, and this can only be provided upon special request from the study database managers. Electronic research charts and regulatory documentation are maintained in an eBinders system hosted by Florence Health Systems under a Business Associate Agreement (BAA) between Johns Hopkins University and Florence. The eBinder Suite is compliant with 21CFR Part 11, HIPAA/the Privacy Rule, and 12CFR part 31 and 812.

# Subject completion/dropout

## Definition of a Dropout

A dropout is defined as any subject who did not come back for at least the week 16 visit as described in the protocol. A subject who returns for the concluding visit foreseen in the protocol is considered to have completed the study participation. Dropouts will be replaced to reach the target enrollment.

## Procedures for Handling Dropouts

The investigator will make a written attempt to contact those subjects who do not return for scheduled visits or follow-up. Information gathered should be described on the Study Conclusion page of the CRF.

## Reasons for Dropout

It should be specified on the Study Conclusion page of the case report form which of the following possible reasons were responsible for dropout of the subject from the study:

- serious adverse event
- non-serious adverse event
- Protocol violation (specify)
- Consent withdrawal, not due to an adverse event
- Migration from the study area
- Lost to follow-up
- Other (specify)

# CLINICAL MONITORING

| The SKCCC Compliance Monitoring Program will provide external monitoring for JHU-affiliated sites in accordance with SKCCC DSMP (Version 6.0, 02/21/2019). The SMC Subcommittee will determine the level of patient safety risk and level/frequency of monitoring. |
| --- |

At University of Wisconsin Carbone Cancer Center (UWCCC) quality assurance and monitoring activities are determined by study sponsorship and risk level of the protocol as determined by the PRMC. All protocols (including Intervention Trials, Non-Intervention Trials, Behavioral and Nutritional Studies, and trials conducted under a Training Grant) are evaluated by the PRMC at the time of committee review. This protocol will be subject to standard monitoring. This means that there will be a review of subject safety at regularly scheduled staff meetings where the results of each subject’s treatment are discussed. The discussion includes the number of subjects enrolled, significant toxicities, dose adjustments, and responses observed. Protocol Summary Reports are submitted on an annual basis by the study team for review by the DSMC. This study will be subject to compliance with the UWCCC Data and Safety Monitoring Plan (version 02/13/2017. Data will be reviewed by Johns Hopkins SMC committee as well as UWCCC compliance team will perform Quality Assurance Reviews and Internal Audits on an annual basis.

# ETHICS AND REGULATORY CONSIDERATIONS

**13.1 Institutional Review Board**

This protocol and an eIRB application and any other required documents will be submitted to the Johns Hopkins IRB and CRO, and their written unconditional approval will be in the possession of the investigator before commencement of the study protocol. No deviations from, or changes to, the protocol will be initiated without prior written IRB approval. The IRB/CRO will be informed of all protocol violations, informed consent changes, or revisions of other documents originally submitted for review. The IRB/CRO will also be informed of serious adverse events occurring during the study, all subsequent protocol modifications, or new information that may affect adversely the safety of the subjects or the conduct of the study. Annual updates will be submitted.

The JHM IRB will be the single IRB of record for this study. A reliance agreement will be fully executed between the Johns Hopkins IRB and the University of Wisconsin, Madison IRB for this protocol.

**13.2 Informed consent**

Information should be given in both oral and written form whenever possible. Subjects will be given ample opportunity to ask about details of the study. Subjects will be informed about the expected risks and benefits, and procedures of the study protocol.

They will be informed of alternative procedures. The informed consent form will be approved by the JHM IRB for both sites. Written consent will be obtained before screening for study enrollment.

Revisions to the informed consent process are being permanently adopted for this research due to the COVID19 pandemic. Depending on institutional and local guidelines, the consenting process can be done in person or via telemedicine visit. Teleconsent will be used as opposed to in person consenting where possible to reduce unnecessary in person encounters specifically for a consent procedure. In the event teleconsent is utilized, participants will be provided with a copy of the Informed Consent prior to the teleconsent meeting either via email, fax, mail or previously provided during an in person visit.

Participants will be given adequate time to consider the research study and ask questions prior to signing the consent form. The consent designee must verify the participant physically signed the consent document either by viewing via video conference, obtaining a photo of the signed consent document; or obtaining verbal confirmation from the participant that he/she signed the consent form or agreed to participate electronically. The participant or LAR will sign and date/time the informed consent document. The document is then mailed, emailed or faxed to the consent designee. The participant will be asked to return the original signed document during their first in person visit. If the Informed Consent form is mailed to the consent designee by the participant the IRB-approved consent designee will sign the copy, which they possess after the participant has acknowledged signature on their copy. Once the original is received by the consent designee the copies will be attached to make a single document. In all other instances, once received, the IRB-approved consent designee signs, dates/times the informed consent document.

At the time of the first clinical encounter post teleconsent, where physician/mid-level provider consent is required, the physician/mid-level provider will review any additional study participant questions and discuss the risks, benefits and alternatives of the study in full detail, completing the physician/mid-level component of the consent process. If physician/Mid-level provider consent occurs remotely in a separate encounter from the main consent process, the previously stated process must be followed for the entire consent conversation. The Documentation of Physician Consent Form is then signed, dated/timed and all components of the consent are combined to one document. After the Informed Consent process is completed, the IRB approved study team member will follow institutional guidelines for uploading research consents to the electronic medical record system, including a note confirming the consent process. The entire consent document is also then filed in the research record.

Once patients sign consent, will be assigned a study ID, and their demographic and clinical information will be entered in a web-based, JHED-authenticated database. This information is also entered in the institutional database CRMS. To maintain confidentiality, the study-specific ID will be used to label all specimens collected and banked during the study. Only the clinical team and program manager will have access to PHI. All other members of the research team will only have access to study-specific IDs.

